#### Recruitment and Screening Procedure

Participants will be recruited from the Prisma Health-Upstate Internal Medicine Clinic who currently have or have had a lifetime history of any major depressive episode. Health care providers at the clinic will identify patients using the *ICD-11* (*International Classification of Diseases, 11th Revision*) codes [41] from the patients’ electronic medical records. Researchers will contact eligible participants and ask for verbal consent before participation in an in-person screening interview with a member of the research team. At this time, the Patient Health Questionnaire (PHQ-9) [42] is to ascertain any current depression symptoms. PHQ-9 scores of 5, 10, 15, and 20 will represent mild, moderate, moderately severe, and severe depression, respectively. If no depression symptoms are currently present, this will also be noted. Participants who meet eligibility criteria will be asked to provide written informed consent before enrolling in this study. Recruitment began in December 2022.

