### Sample Size

The total sample size of our trial is expected to be 128 individuals with 64 participants placed into each group. This was estimated by a 2-tailed *t* test using GPower 3.1 (Informer Technologies, Inc) software. Our calculation of sample size depended on (1) the level of significance (α error probability), which was set as .05 based on Ronald A Fisher’s suggestion [55]; (2) the expected effect size, which was set as *d*=0.5, according to Cohen classification that “a medium effect of .5 is visible to the naked eye of a careful observer” [56]; (3) the expected power of this study (1–β error probability), which was set as 0.8 based on Cohen theory [57] because we failed to obtain support from previous similar studies; and (4) the allocation ratio (N2/N1), for which we expect number of participant in treatment group and control group to be the same.

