### Randomization

Consenting participants will be randomized 1:1 to either group 1 or group 2 via the randomization function found in Qualtrics. This will be conducted by the principal investigator (PI). Once the number of participants has reached 7-12 individuals for both group 1 and group 2, this study will commence. This will proceed continuously until the expected sample size of 128 individuals is reached, or 4 years have elapsed. The implementation of this process will be overseen by the clinical research team.

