### Statistical Methods

#### Primary Outcomes

An intent-to-treat method will be used to conduct the primary analyses. By comparing the baseline and demographic variables between groups, the randomization success will be determined. With a random intercept for a cluster of individuals, generalized linear mixed effects models (GLMMs) will be used [58] to assess the effects of MBCT on depression and psychiatric distress symptoms (hypothesis 1). Week 8 will be the primary end point for this assessment. The covariates measured at TI that are relevant but not balanced between group 1 and group 2 will be incorporated into all models. Additionally, all analysis models will include clinical site level as a fixed effect. GLMMs will be used to test the association between MBCT psychiatric distress (hypothesis 2), in addition to gains sustained at an 8-week follow-up (hypothesis 3).

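### Covariates are chosen by observed baseline imbalance, so the TI score of each outcome is not a fixed covariate of the week-8 model; precision is lost and the model depends on the data

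*Protocol article*

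**What the plan says.** Three statements under Statistical Methods, Primary Outcomes, set the adjustment.

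- A balance check comes first: "By comparing the baseline and demographic variables between groups, the randomization success will be determined".
- Its result decides the covariates: "The covariates measured at TI that are relevant but not balanced between group 1 and group 2 will be incorporated into all models".
- One term is fixed in advance: "all analysis models will include clinical site level as a fixed effect".

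The same section makes week 8 the primary end point and gives the mixed models a random intercept for a cluster, which it does not define. The next section, on secondary outcomes, moderators and mediators, uses baseline depression only as a moderator in a separate model. Nowhere is the TI value of an outcome named as a covariate of that outcome's primary model.

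On sites, Recruitment and Screening Procedure says "Participants will be recruited from the Prisma Health-Upstate Internal Medicine Clinic", whereas Eligibility Criteria also admits Greenville residents and patients of partnering organizations. On cohorts, Randomization lets a batch start once each group has 7 to 12 people, and then: "This will proceed continuously until the expected sample size of 128 individuals is reached, or 4 years have elapsed".

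**The concern.** Under randomization, any baseline difference between groups is due to chance. Comparing the groups cannot show whether randomization worked, and it is a poor guide to which covariates to use. A covariate earns its place by predicting the outcome. The TI score of the same instrument is usually the strongest predictor available, and under this rule it is left out unless it happens to be unbalanced.

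Two things are at stake. The primary estimate is less precise than the collected data allow. The primary model is also unknown until someone has judged which variables are relevant and unbalanced, with no stated criterion for either. This is not a detail left to an analysis plan. The article states a rule, and an analysis plan that fixed the covariates would have to contradict it.

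**Working it through.** **Inputs from the article (Sample Size).** Two-sided α: "the level of significance (α error probability), which was set as .05". Test: "This was estimated by a 2-tailed *t* test using GPower 3.1". Effect: "the expected effect size, which was set as *d*=0.5", so SD = 1. Target power 0.80, 64 per group, 1:1.

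**Assumptions, not in the article.** The correlation r between the TI and week-8 scores, taken as 0.3, 0.5 and 0.7. Imbalance is read as p<0.05 in a two-sample t test of the baseline score.

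**Step 1. The plan's own figure.** Noncentrality is d·√(n/2) = 0.5·√32 = 2.83 on 126 degrees of freedom. Exact noncentral-t power is 0.8015 at n=64 and 0.7952 at n=63. The stated 128 reproduces, as a calculation without covariates.

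**Step 2. Variance factor of each analysis, relative to the unadjusted week-8 comparison.**

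- Unadjusted week-8 score: 1.
- Change from TI to TII: 2(1−r), that is 1.40, 1.00 and 0.60. A mixed model with TI as a repeated outcome and a group × time contrast amounts to this.
- Week-8 score adjusted for TI score: 1−r², that is 0.91, 0.75 and 0.51.

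The effective standardized difference is 0.5/√(factor). For the adjusted analysis this is 0.524, 0.577 and 0.700.

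**Step 3. Power at 64 per group.** The imbalance rule was simulated, with 40,000 trials per setting. The other rows are exact noncentral-t values.

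| Analysis | r=0.3 | r=0.5 | r=0.7 |
|---|---|---|---|
| Unadjusted | 0.801 | 0.801 | 0.801 |
| Change from TI | 0.660 | 0.801 | 0.952 |
| Adjust only if unbalanced | 0.805 | 0.813 | 0.820 |
| Prespecified TI covariate | 0.837 | 0.900 | 0.976 |

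The simulation gave 0.835, 0.900 and 0.974 for the last row, which agrees. With the prespecified covariate, 80% power would need 118, 98 or 68 participants in total instead of 128.

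**Step 4. Spread of the estimate.** The simulated SD under the imbalance rule against the prespecified covariate is 0.1744 v 0.1689, 0.1701 v 0.1531 and 0.1645 v 0.1265. The squared ratios are 0.94, 0.81 and 0.59. Prespecifying therefore cuts the variance by about 6%, 19% and 41%.

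**Step 5. Type I error of the imbalance rule.** Simulated with no effect: 0.048, 0.043 and 0.035. The rule is slightly conservative.

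**Step 6. How readily the rule changes the model.** The article lists 11 demographic items. If they were independent and judged at 5% (both assumed), the chance that at least one is flagged is 1−0.95¹¹ = 0.43. This is only indicative. The article gives no threshold, requires relevance as well, and the items are correlated.

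**The case against.** **The baseline may already be in the model.** Hypotheses 1 and 2 concern reduction from TI to TII, so a repeated-measures model containing TI is a natural reading. That is fair, and the change-score row covers it. It is still below baseline adjustment at every r, and at r=0.3 it falls below the unadjusted comparison.

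**The planned power is met anyway.** The stated sample size is right for an unadjusted comparison, and the gain is small if r is low: about 3 points over the imbalance rule at r=0.3. Both statements stand. The point is about efficiency and prespecification, and a reader should not infer that the sample size is wrong.

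**Analysts are masked.** The Blinding section keeps analysts unaware of assignment until analysis ends. This limits deliberate selection. It does not fix the model, because imbalance between two coded groups is still visible.

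**Stronger readings that the article does not support:**

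- *The rule inflates false positives.* In the single-covariate simulation it does not.
- *The site term is constant.* One clinic is named, so this is likely. Partnering organizations are mentioned in the plural, so it is not certain. If there is only one site, the term is redundant and does no harm.
- *Cohort variation is left in the error term.* The models carry random effects for a cluster, which may be the therapy group or start cohort. What can be said is that the cluster is undefined. A random intercept for a therapy group nested within arm would model correlation but would not adjust the comparison for cohort. No gain from a cohort term has been quantified.

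**Conclusion.** The point holds as a matter of precision and prespecification. At 64 per group and d=0.5, a prespecified TI covariate gives power of 0.84, 0.90 and 0.98 for r of 0.3, 0.5 and 0.7. The stated rule gives 0.80 to 0.82, so it recovers little of what the baseline score offers. The gain over the rule is about 3, 9 and 16 points. Its size rests on r, which the article does not give, and on reading imbalance as p<0.05. Its direction does not depend on r within the range examined, whether the model is taken as a week-8 comparison or as change from TI. The change should be made, but the trial is not invalid without it. The remarks on site and cluster are requests for definition, not demonstrated errors.

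**What to change.** - Name the TI value of the analysed outcome as a covariate in every outcome model.
- Delete covariate selection on imbalance and the check of randomization success. Report baseline characteristics by group descriptively.
- Keep models with any other covariates as sensitivity analyses.
- Keep the site term only if more than one site recruits, and say what counts as a site.
- State whether the cluster is the therapy group or the start cohort. A start-cohort term is an optional addition. With 14 to 24 people per batch, 128/24 to 128/14 is roughly 6 to 9 cohorts, or about 5 to 8 degrees of freedom.

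No new data, visits or participants are needed. The cost is a revision of the text and, because the article requires it for protocol changes, a formal amendment to the review board. The abstract says data analysis began in February 2024, while recruitment may run to September 2026. The amendment should therefore be dated and should state what outcome data by group had been seen when the covariates were fixed.

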#### Secondary Outcomes, Moderators, and Mediators

GLMMs will be used to assess the association between MBCT and the secondary outcomes of perceived stress and mindfulness skills (hypothesis 4). Potential moderators of the effect of MBCT, namely treatment history, traumatic life events history, baseline depression, and their interaction with MBCT, will be looked at in their own GLMMs. Using regression coefficients, the role of moderators that these variables may play will be assessed.

Using the PROCESS macro [59] in SAS (SAS Institute), the mediators, extent of mindfulness self-practice, and executive functioning skills (hypothesis 5), will be examined via the product of the coefficient method. This will be limited to the first phase of this study lasting 8 weeks. Further, 2 separate GLMMs will be used to assess how the primary and secondary outcomes may be indirectly influenced by MBCT. By regressing the mediator and outcome, respectively, on MBCT, and controlling for the mediators as well as applicable covariates, the indirect effects of MBCT on outcomes will be examined. Parallel multiple mediator models in addition to serial multiple mediator models will be used to conduct sensitivity analysis. To examine if MBCT effects will be sustained through 8 weeks postintervention (hypothesis 3), linear mixed-effects models will be used with main effects consisting of treatment group, time, group × time interaction, and nested random effects for subjects and cluster. A regression parameter associated with group × time interaction at 0 will be the null hypothesis. This acts as an equivalent for assessing the carryover effect [60]. If rejected, there is support that the effects of the intervention remain after 8 weeks have elapsed. An imputation method will be used to address any data that are missing.

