## Methods

### Study Design

Our study plans to examine how MBCT delivered via the web may affect primary and secondary outcomes for individuals with a history of depression. It will also assess mediators, moderators, and the sustainability of the intervention. The following hypotheses will be assessed among program participants in the intervention group as compared to a waitlist control group, and within groups compared from pre- to postintervention.

The MBCT intervention group will show a greater reduction in depressive symptoms from TI to TII, compared to the waitlist group.The MBCT intervention group will show a greater reduction in psychiatric distress symptoms from TI to TII compared to the waitlist group.The MBCT intervention group will sustain gains through the 8-week follow-up period at TIII.The MBCT intervention will improve secondary outcomes, such as:perceived stressfacets of mindfulnessThe MBCT intervention will improve the skills associated with mechanisms of change for individuals with a history of depression, and these skills will act as mediators between MBCT and primary and secondary outcomes:extent of mindfulness self-practiceexecutive functioning skillsThe format delivered via the web will meet feasibility aims measured by adherence, retention, attendance, and engagement.

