#### Eligibility Criteria

Participants in this study must (1) be aged 18 years at a minimum, (2) speak English fluently, (3) have sixth grade and above literacy, (4) be willing to share contact information (home address, phone number, or email), (5) have no current mindfulness practice, (6) be Greenville residents or persons who are patients of the partnering organizations in our study, and (7) have current or a lifetime history of any major depressive episode. Study exclusion criteria include (1) current psychosis, dementia, moderate to severe traumatic brain injury, pregnancy, or active suicidality; (2) persistent antisocial behavior; (3) persistent self-injury requiring clinical management; (4) an acute episode of a substance use disorder episode (met 2 or more substance use disorders criteria in the past 2 weeks); (5) previously completed or currently attending an MBI; and (6) are currently younger than 18 years, are non–English speakers, or have a literacy lower than sixth grade.

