#### Intervention Procedures

The intervention will be delivered by 3 Licensed Clinical Social Workers who have previously undergone MBCT teacher training and become certified instructors. The intervention will consist of 8 weekly 2-hour group therapy sessions. All sessions will be delivered to a group of up to 12 participants and will take place over Zoom (Zoom Video Communications, Inc). The minimum number of participants needed to proceed with each intervention program is 7 individuals. Certified instructors will follow the standardized MBCT protocol developed by Segal et al [43] (see Textbox 1 for the outline of each session).

Mindfulness-based cognitive therapy program outline per Segal et al [43].Session 1: Awareness and automatic pilotSession 2: Living in our headsSession 3: Gathering the scattered mindSession 4: Recognizing aversionSession 5: Allowing or letting beSession 6: Thoughts are not factsSession 7: How can I best take care of myself?Session 8: Maintaining and extending new learning

MBCT integrates training in mindfulness meditation and cognitive-behavioral methods. It teaches skills designed to increase awareness of internal reactions that trigger depressive symptoms, such as depression-related rumination and negative thoughts, and provides techniques to detach from these dysfunctional cognitive processes [19]. In the first half of the program, participants will focus on learning the principal tenets of mindfulness. They will explore central themes about the tendencies of the mind to habitually engage with thoughts, which produces an array of feelings and emotions. In the latter half of the program, participants will begin the practice of becoming aware of thoughts as they arise, thereby witnessing habitual patterns that may lead to unpleasant feelings or emotions [43]. Outside of the sessions, participants will be assigned daily homework exercises and given handouts as well as audio recordings to use in their mindfulness practice. Participants who miss a session will be contacted by the research team to determine if they would benefit from medical or psychiatric assistance and to assess any barriers to upcoming sessions.

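### The two-arm mediation test for self-practice rests on non-randomised differences in homework uptake within the MBCT arm, and the stated covariate rule does not deal with that

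*Protocol article*

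**What the plan says.** Hypothesis 5 (Study Design) names extent of self-practice and executive functioning as skills that MBCT improves, and states that "these skills will act as mediators between MBCT and primary and secondary outcomes". Under Secondary Outcomes, Moderators, and Mediators, both "will be examined via the product of the coefficient method. This will be limited to the first phase of this study lasting 8 weeks". Mediator and outcome are each regressed on MBCT, so both arms enter.

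The practice variable is defined under Extent of Mindfulness Self-Practice. It is self-reported days per week of practice apart from the study sessions. The Engagement section uses the same group of items as a feasibility measure.

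Three other statements bear on how this variable will behave:
- Eligibility Criteria: every entrant must "have no current mindfulness practice", and anyone who has completed or is attending a mindfulness programme is excluded.
- Intervention Procedures: outside the sessions, "participants will be assigned daily homework exercises and given handouts as well as audio recordings to use in their mindfulness practice".
- Trial Design: in the first 8 weeks, group 2 receives treatment as usual.

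On adjustment, the Primary Outcomes part of Statistical Methods brings into all models those baseline (TI) covariates that are relevant and differ between the arms. The mediation paragraph adds only that applicable covariates will be controlled.

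**The concern.** A product-of-coefficients test multiplies path a (treatment to mediator) by path b (mediator to outcome, given treatment). Path a is protected by randomisation. Path b is not.

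Here path a is close to settled in advance, because one arm is told to practise daily and the other is not. A significant path a then says little more than that homework was done. The test turns on path b, and nearly all the variation in practice that informs path b lies among MBCT participants who chose how much to practise. If those with a better prognosis practise more, path b is non-zero even when practice does nothing.

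A covariate rule driven by imbalance between arms looks in the wrong place. A factor can be perfectly balanced between arms and still determine who practises within one of them. At stake is the causal reading of hypothesis 5, since the Conclusions and Discussion promise insight into causal pathways. The primary analysis is not affected.

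**Working it through.** **Plan's own figure.** Sample Size gives a two-tailed t test, α = 0.05, d = 0.5, power 0.8, 64 per arm. The noncentrality is d·√(n/2) = 0.5·√32 = 2.83 on 126 degrees of freedom, so power is 0.801 at 64 per arm (0.795 at 63). The total of 128 reproduces. The mediation test has no stated figure, so the check uses 64 per arm and d = 0.5.

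**Assumptions (not in the documents).** MBCT practice has mean 4.5 and SD 1.8 days, capped at 0–7. On the waitlist, 10% report 1 day and the rest 0, giving mean 0.1 and variance 0.1 × 0.9 = 0.09. Practice has no causal effect.

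**Models.** M = i₁ + aX + e₁ and Y = i₂ + c′X + bM + e₂. Sobel z = ab / √(a²·se_b² + b²·se_a²), which equals z_b / √(1 + (z_b/z_a)²).

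**Step 1, path a** (ignoring the cap). a = 4.5 − 0.1 = 4.4. The pooled within-arm SD is √((3.24 + 0.09)/2) = 1.29. se_a = 1.29·√(2/64) = 0.228, so z_a = 4.4/0.228 = 19.3. With z_b = 2, Sobel z = 2/√(1 + (2/19.3)²) = 1.99. The test of ab is in effect the test of b. In simulation, path a was significant in 100% of trials.

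**Step 2, where b comes from.** The MBCT arm's share of within-arm practice variance is 3.24/(3.24 + 0.09) = 97%. With MBCT SD 1.5–2 and waitlist SD 0.3–0.8 (nominal values), it runs from 2.25/(2.25 + 0.64) = 78% to 4/(4 + 0.09) = 98%.

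**Step 3, collinearity.** r² = (4.4/2)² / ((4.4/2)² + 1.665) = 4.84/6.505 = 0.744, so the variance inflation is 1/(1 − 0.744) = 3.9. With the cap, simulation gives 4.3 to 4.5.

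**Step 4, share of trials with a significant practice effect when the true one is zero** (3000–4000 simulated trials per cell). The confounder correlates 0.6 with outcome. The last three columns are two-arm results.

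| Confounder–practice correlation | Two-arm, unadjusted | Within-MBCT slope, unadjusted | Adjusted only if arms differ at p < .05 | Always adjusted, TI outcome correlates 0.7 with confounder | Always adjusted, confounder fully captured |
|---|---|---|---|---|---|
| 0 | 5–5.5% | 5% | – | 5% | 4–5% |
| 0.3 | 28% | 28–29% | 28% | 13% | 5% |
| 0.5 | 65–66% | 66–68% | 61–64% | 26% | 5–5.5% |

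The p < .05 criterion is one reading of the protocol's imbalance rule.

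**Step 5, sensitivity to the assumed distribution.** MBCT mean 3–5 days and SD 1.5–2; waitlist mean 0–0.3 and SD 0.3–0.8. Size without confounding is 4.6–5.3%. Power under full mediation without confounding is 21–73%. False mediation is 11–14% when the confounder correlates 0.3 with both practice and outcome, and 52–70% at 0.5 with both.

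**Step 6, the other mediator.** Take a mediator that varies in both arms, has no causal effect, and carries the same confounding as in step 4. At an assumed 0.6 SD arm shift it is falsely significant in about 30% or 74% of trials.

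**The case against.** The strongest reply is that a mediator moved by treatment is what mediation requires, so a strong path a is a precondition and not a fault. That stands. A reader might infer that the test cannot show mediation at all. The documents and the calculation do not support this: size is correct without confounding, and there is some power.

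A reader might also infer that waitlist practice is zero by design, or that the variable merely records receipt of MBCT. Neither is stated. Eligibility governs practice at entry only, nothing bars waitlist participants from starting, and the variable is a graded count that excludes sessions. The Discussion gives a dose-dependent rationale for it.

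The false positives come from mediator-outcome confounding, which is not special to practice. Executive functioning is equally exposed, and an unadjusted within-MBCT slope is no better than the two-arm test. Both points stand, so removing self-practice would mostly relabel the problem. An MBCT-by-practice interaction would be barely estimable if waitlist practice is near zero.

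Two further inferences fail. With practice in the model, power for the direct effect falls from 80% to about 28% in the unconfounded case, but the plan describes no direct-effect test and nowhere says that a non-significant direct effect means full mediation. Nor is it shown that practice blurs the executive-functioning estimates: when the two mediators shared only the confounder, adding practice left the other's standard error unchanged (ratio 1.00).

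Finally, a condensed article may leave the covariate set to a fuller document, so its absence is not the point. What remains is the rule that is written, which selects covariates by between-arm imbalance. The reference to applicable covariates supplies no other criterion.

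**Conclusion.** The concern holds in a limited form. As specified, the self-practice test cannot separate mediation from confounded adherence. It rests on a non-randomised practice-outcome slope drawn almost entirely from the MBCT arm, and selecting covariates by imbalance between arms does not protect that slope.

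The size depends on the confounding: about 5% false mediation with none, 11–14% when it is modest, and 28% to 70% in the stronger scenarios. All of these rest on assumed practice distributions and confounder strengths, because the documents give neither. The direction does not depend on a waitlist value of exactly zero. The point concerns one mechanistic hypothesis; the test of MBCT's effect at week 8 stands apart from it.

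**What to change.** 1. In the self-practice and the executive-functioning mediator models, always adjust for the TI value of the outcome and for prespecified TI prognostic covariates, whether or not they differ between arms.
2. Add a dose-response analysis of practice days within the MBCT arm, with the same adjustment, labelled as non-randomised.
3. State that a significant self-practice indirect effect alone will not be reported as causal support for hypothesis 5.

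Self-practice can stay in the mediator models, and no interaction term is needed. The adjustment reduces the problem and does not remove it: in the table, 28% falls to 13% and 65% to 26% when TI outcome correlates 0.7 with the confounder, and about 5% is reached only if the confounder is fully captured.

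The cost is analysis wording and a little extra analysis. The TI outcome values and the practice items are already in the assessment schedule. The downside is a more cautious conclusion for one of the two named mediators.

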We also hope to examine the impact of MBCT on secondary outcomes, including perceived stress and facets of mindfulness. There is increasing evidence in support of perceived stress being positively correlated with the risk of developing depression [64,65]. This may be due to increased activity in the superior frontal gyrus which plays an important role in emotional regulation and cognitive control, with higher spontaneous activity in this region being possibly associated with psychopathologies such as MDD, posttraumatic stress disorder, and social anxiety disorder [66]. If MBCT has a positive impact on perceived stress, this study will add to the understanding of the causal pathway between MBCT, perceived stress, and depressive symptoms. Similarly, given that facets of mindfulness are inversely correlated with components of depression [67], this study can add to the evidence supporting the role that MBCT may play on that causal pathway also.

Through measurement of the extent of mindfulness self-practice and executive function, we hope to better understand the causal pathways between MBCT and depression symptoms. The positive effects of mindfulness practice have been purported to follow a dose-dependent pattern. This may be due to increased functional connectivity within various brain regions [68]. As such, it would be important to assess the role of mindfulness self-practice outside of the dedicated intervention time and its effects on depression. Finally, executive functioning has been shown to have an important influence on emotional regulation abilities [69,70]. The application of MBIs has been shown to be a viable means of improving certain aspects of executive function [71]. Thus, examining executive functioning could provide important insight into MBCT’s ability to influence emotional regulation and depression symptoms.

We will also be able to look at moderators and correlates of intervention outcomes, such as intervention adherence and mental health history, to determine factors that could improve or detract from intervention success.

Overall, this study will generate valuable insights elucidating the possibility of future studies with larger scopes and more elaborate study designs. These may consist of multiple evidence-based comparisons and longer postintervention follow-ups.

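### The only covariate rule that reaches the hypothesis 5 mediation models selects on between-arm imbalance, which does not control confounding of the mediator-to-outcome path

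*Protocol article*

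**What the plan says.** Three statements in the protocol article's Statistical Methods bear on this.

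- **Primary Outcomes**, covariate selection: "The covariates measured at TI that are relevant but not balanced between group 1 and group 2 will be incorporated into all models". The same paragraph adds that "all analysis models will include clinical site level as a fixed effect".
- **Secondary Outcomes, Moderators, and Mediators**, method: the two mediators, self-practice and executive functioning, "will be examined via the product of the coefficient method". On the time window: "This will be limited to the first phase of this study lasting 8 weeks". The only post-randomisation visit in that window is TII, so mediator and outcome are both taken there.
- **Same section**, covariates: by regressing mediator and outcome "on MBCT, and controlling for the mediators as well as applicable covariates, the indirect effects of MBCT on outcomes will be examined". No list or definition follows.

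The sensitivity analyses named for mediation are these: "Parallel multiple mediator models in addition to serial multiple mediator models will be used to conduct sensitivity analysis". The Discussion gives the purpose: "we hope to better understand the causal pathways between MBCT and depression symptoms".

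Nothing in the article names the TI mediator score or the TI outcome score as a covariate in the hypothesis 5 models. Nothing rules them out either.

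**The concern.** The product of coefficients multiplies path a (MBCT to mediator) by path b (mediator to outcome, given MBCT). Randomisation protects path a but not path b, because nobody is randomised to a level of executive functioning.

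Between-arm balance tells us about confounding of the randomised contrast. It says nothing about path b. Suppose people who enter with more executive deficits also enter with higher PHQ-9 scores, and both tend to persist. Then TII executive functioning and TII PHQ-9 are correlated within each arm even if neither affects the other. That holds when the two TI scores are identically distributed across arms, so a rule that looks for imbalance would usually pass over them. The better the randomisation works, the less likely the rule is to pick up these confounders.

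The parallel and serial models do not help, because they rearrange the mediators and add no baseline confounder.

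At stake is a positive finding on hypothesis 5, and any reading of it as a causal pathway, when no mediation exists. The week-8 primary comparison and the sample size are unaffected.

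**Working it through.** **1. The plan's own figure.** The article gives no number for the mediation analysis. Its sample size does reproduce: d = 0.5, two-sided alpha 0.05 and power 0.80 give 63.77, so 64 per arm and 128 in total, with power 0.801.

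**2. Inputs.** From the article: N = 128, 64 per arm, alpha 0.05. Assumed, because the article gives no values:

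- TI mediator-outcome correlation r0 = 0.3 or 0.5
- TI-to-TII stability s = 0.5 or 0.7 for both scores
- MBCT shift in the mediator of 0.5 SD
- scale reliability of 1.0 or 0.8
- true effect of mediator on outcome of zero

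The arms are balanced at TI in expectation throughout.

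**3. Apparent path b without TI scores.** With unit-variance scores, the within-arm TII covariance of mediator and outcome is s² × r0, so the apparent b is s² × r0. For r0 = 0.5 and s = 0.7 it is 0.49 × 0.5 = 0.245, although the true value is 0.

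**4. How often mediation is declared.** Take mediation as declared when paths a and b are both significant.

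- Path a is a 0.5 SD difference with 64 per arm, so its power is 0.801.
- Path b has an expected t of about b√125 / √(1 − b²). For b = 0.245 this is 0.245 × 11.18 / 0.970 = 2.83, which gives power of about 0.807.
- The product is 0.801 × 0.807 = 0.65.

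With reliability 0.8 on both scales, b shrinks by a factor of 0.8 and the shift becomes 0.5 × √0.8 = 0.447 observed SD, for which the power is 0.709.

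| r0 | s | Apparent b | Calculated, reliability 1.0 | Simulated, reliability 1.0 | Calculated, reliability 0.8 | Simulated with both TI scores, reliability 1.0 |
|---|---|---|---|---|---|---|
| 0.3 | 0.5 | 0.075 | 10.7% | 10.1% | 7.3% | 4.6% |
| 0.3 | 0.7 | 0.147 | 30.7% | 30.5% | 18.6% | 5.0% |
| 0.5 | 0.5 | 0.125 | 23.3% | 22.0% | 14.4% | 5.4% |
| 0.5 | 0.7 | 0.245 | 64.6% | 66.4% | 43.1% | 4.1% |

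The simulated columns come from 800 trials per setting, using a Monte Carlo interval for a × b. Runs based on joint significance gave about 63% in the top setting, so 63% to 66% is one result within simulation error and choice of test.

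**5. Effect of adjustment.** Adding the TI outcome score, alone or with the TI mediator score, brings the rate to about 3% to 6%. Single settings with only one TI score reached about 7%.

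**6. When the problem disappears.**

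- r0 = 0: apparent b is 0 and there is no bias.
- No MBCT effect on the mediator: path a is significant in about 5% of trials, so the joint rate cannot exceed about 5% (simulated maximum 5.2%, even at r0 = 0.7).

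**7. Change scores instead of raw TII scores.** With TI-to-TII change in both variables and no covariates, the rate is about 4% to 23%. In the top setting with perfect reliability it falls from about 64% to 13%. At r0 = 0.5 and s = 0.5 it hardly moves (22% to 23% either way).

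**The case against.** The strongest reply is about the text. A reader might infer that the hypothesis 5 models adjust only for unbalanced variables and that TI scores are left out. The article does not say so. The rule under Primary Outcomes states what will be included and excludes nothing, and the phrase about applicable covariates is open enough to cover TI scores. That reply stands against the stronger reading.

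A second reply is that this is a condensed article, and a covariate list belongs in the analysis plan. For a mere omission that would be decisive. But the article is not silent: it fixes a selection criterion for all models, and that criterion is unsuited to path b. An analyst following it has no instruction to include the TI scores.

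Third, the size rests wholly on assumed inputs and on regressing raw TII scores, a form that the article does not fix. This is correct. Change scores reduce the problem without reliably removing it.

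Fourth, the persistence argument does not suit self-practice. Current practice bars entry (Eligibility Criteria), so TI practice should be near zero and no figure above applies to it. This also stands. For that mediator the relevant confounder is the TI outcome, since baseline depression may affect both how much people practise and how they score at TII.

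Finally, the Discussion's causal wording is a hope, not a stated conclusion, and hypothesis 5 is not the primary question.

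**Conclusion.** The concern holds in a limited form. The one covariate rule that reaches the hypothesis 5 models selects on between-arm imbalance. That does not control mediator-outcome confounding, and nothing in the article requires the TI scores that would help to do so. For executive functioning, false mediation would be declared in roughly 7% to 63% of trials under the assumed ranges with raw TII scores, against about 3% to 6% with TI adjustment.

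Two conditions must both be met: MBCT moves the mediator, which hypothesis 5 itself predicts, and the TI mediator and TI outcome are correlated. The article gives a size for neither. It would therefore be wrong to say that the plan will report stable trait correlation as mediation; it leaves that possible. Adjusting for TI scores also does not make path b randomised: unmeasured confounding would remain.

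**What to change.** State that every hypothesis 5 model, in both the mediator equation and the outcome equation, includes the TI value of the outcome as a fixed covariate whatever its balance between arms. For executive functioning, add the TI value of the mediator on the same terms. For self-practice, include at least the TI outcome score. State also that between-arm imbalance is not used to choose covariates for mediation.

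The cost is one sentence and one or two degrees of freedom per model; N stays at 128. PHQ-9 is measured at TI (Baseline Depression Symptoms). Collection of the executive functioning scale at TI is inferred from the general assessment schedule, because Figure 2 is not shown, and should be confirmed. If it is not collected then, the TI outcome score alone does most of the work in the settings examined.
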